### Study population

All patients aged 60 years and older with an unplanned hospital admission are eligible for inclusion if they meet the inclusion criteria. The inclusion criteria are polypharmacy (defined as using ≥5 medications chronically), using at least two medications from the triggerlist and the ability to give informed consent.

Patients with a life expectancy of less than 3 months (assessed by the involved practitioners); patients with an intentional auto-intoxication; and patients treated with cytostatic will be excluded.

### Outcomes

#### Primary outcome

The primary outcome of this study is hospital readmission within 1 year after study inclusion.

#### Secondary outcomes

The secondary outcomes of this study are (I) mortality within 1 year after study inclusion; (II) the number of emergency department visits; (III) the number of nursing home admissions; (IV) time to hospital readmission; and (V) the number of hospital readmissions after 30 and 180 days. Next, we will analyze whether the readmission is (probably) medication-related. Whether a hospital readmission is medication-related will be defined afterwards, using the triggerlist. The information for secondary outcomes will be obtained from the electronic prescription system and electronic patient record. Furthermore, quality of life (QoL) and costs measured from a societal perspective will be assessed at baseline (hospital discharge) and after 3, 6 and/or 12 months (see questionnaires).

### Study procedures

Three times a week the electronic prescription system is used to select the patients of 60 years and older admitted to the hospital with polypharmacy and at least two medications from the triggerlist. A research nurse will visit the patient at the ward and assess whether the patient is eligible for inclusion. The patients will receive written information about the study and after 2 days the research nurse will visit them again. Then they have to indicate whether they are willing to participate by signing informed consent. Inclusion already started in April 2019 and will finish in August 2022.

After inclusion, patients will be randomized into the intervention or the control group by using a digital randomization system with block randomization. The randomization is blinded for the patients, the GP and the pharmacist. Figure 1 illustrates the study design and randomization procedure.

**Fig. 1 Fig1:**
[figure not shown]
Study design and randomization procedure of CHECkUP. Legend: MOP: Medication Optimisation Profile; GP: General practitioner; CDSS: clinical decision support system; EQ-5D-5L: EuroQol-5D-5L; RUM: Resource Use Measurement

### CDSS

In the present study we use a CDSS (we use the Clinical Rule Reporter, developed by Digitalis) to optimise medication on a continuous basis, ensuring that new medication interactions or problems, e.g. related to comorbidity, laboratory data (renal function) are quickly identified. This software has been validated and is currently used in multiple settings i.e. hospital and nursing homes [24–26]. The CDSS analyses the pharmacotherapy of patients using data regarding the patient’s medication, patient characteristics such as age, sex and laboratory values, and different guidelines/criteria specific for medication assessment, such as the START/STOPP criteria [24, 25, 27]. Combined with the patient’s medication list and characteristics, these different guidelines and criteria are summarized in 151 different clinical rules (see Additional file 1, Table S1). These clinical rules aim to optimize the medication list and gives clinically relevant recommendations, such as lab orders, dose adjustment, stop medication. Then, the different recommendations per patients are summarized into a Medication Optimization Profile (MOP). Figure 2 shows a schematic overview of the CDSS and an example of how different characteristics can trigger different recommendations.

**Fig. 2 Fig2:**
[figure not shown]
Schematic overview of the CDSS and example. Legend: When running the CDSS, the patient’s medication list (1) is combined with his/her characteristics (2), such as age, sex and laboratory values (renal function, potassium level etc.). Next, these data are run through the 225 different clinical rules (3). When no clinical rules apply, a green signal is given (4) and no further actions are required (**C**). When clinical rules do apply a red signal is given and clinical recommendations (5) will be sent to the GP and/or pharmacist. The figure also shows an example of a 75 year-old female that is prescribed digoxin. The clinical rule about ‘potassium and digoxin’ is applied and different scenario’s in which the potassium level is unknown (**A**), 6.2 mmol/L (**B**) or 4.7 mmol/L (**C**) lead to different clinical recommendations with the recommendation to order lab (**A**), correct electrolyte imbalances or dose adjustment (**B**) or no action is required (**C**), respectively. This figure was created using Servier Medical Art templates, which are licensed under a Creative Commons Attribution 3.0 Unported License; https://smart.servier.com

### Participation GPs and pharmacist

During the 1 year study period, the patient’s own GP and pharmacist receive the MOPs, to optimize pharmacotherapy. All GPs and pharmacists in the region were approached to voluntarily participate in the study. Only patients of GPs and pharmacists who had indicated to take part in the study will be able to participate.

### Intervention group

Patients included in the intervention group will undergo continuous medication checks using the CDSS once the patient is discharged. At discharge, the GP and pharmacist will receive their patient’s MOP. From then on the MOPs will be sent on a weekly basis for the period of 1 year. The GPs and the pharmacists can access this MOP and make necessary changes to the medication when appropriate. When they decide not to follow the recommendation made by the CDSS they are asked to indicate a reason.

### Control group

The control group will receive standard care. The GPs and the pharmacists are not informed of which patients are participating as control. Therefore the GPs and pharmacists are blinded for this part of the study. The CDSS will also generate a MOP at discharge for patients in the control group. However this will not be sent to the patient’s GP and pharmacist and is only generated for analysis at the end of the study.

### Questionnaires

All patients (both intervention and control group) will be sent standardized questionnaires about the quality of life (EuroQol 5D-5L (EQ-5D-5L)) and costs from a societal perspective (Resource Use Measurement (RUM)) at hospital discharge, and after 3, 6 and/or 12 months after inclusion [28, 29]. The research nurse will determine whether the included patient will receive the second RUM questionnaire at 3, 6 or 12 months after inclusion, in order to make sure that the groups are equal. The patients will receive the questionnaires via email and receive an automatically generated reminder after 1 week. The questionnaire must be completed within 1 month.

### Sample size calculation

Based on a pilot-study the readmission rate for this selected group is estimated to be 20% [30]. The aim of this study is to reduce the readmission rate from 20 to 15%. To demonstrate this reduction (power 80%; significance level 5%; dropout 20%) at least 1130 evaluable patients are necessary per group. The target population is 2400 patients. The study will include 1200 patients in the intervention group and 1200 patients in the control group divided over the two hospitals with a minimum of 600 patients per location (300 per group).

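### The 1130 per group labelled evaluable already contains the 20% dropout allowance: it is the number to randomise, and about 906 evaluable are needed

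*Protocol article*

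**What the plan says.** The Primary outcome section of the protocol article defines a binary endpoint: "The primary outcome of this study is hospital readmission within 1 year after study inclusion". The Sample size calculation section takes a control rate of 20% from a pilot study and sets the target effect: "The aim of this study is to reduce the readmission rate from 20 to 15" per cent. It then gives the requirement: "To demonstrate this reduction (power 80%; significance level 5%; dropout 20%) at least 1130 evaluable patients are necessary per group". The recruitment target follows: "The study will include 1200 patients in the intervention group and 1200 patients in the control group", 2400 in all. The Economic evaluation section repeats 1200 per group.

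The section does not say whether the 5% level is one-sided or two-sided, and it does not name the sample size formula.

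**The concern.** Dropout is listed among the inputs that lead to 1130, yet the result is described as a count of evaluable patients. It cannot be both. A number inflated for dropout is a number to enter into the trial; the evaluable number is what remains after dropout.

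The label also puts the section at odds with its own target. If 1130 evaluable patients per group really were necessary and 20% were lost, 1200 per group would not be enough.

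At stake is the yardstick for judging whether the trial reached its planned size. Someone comparing the number analysed with 1130 would set the bar 224 per group too high (1130 − 906). They could then call the trial short when it had met its power target.

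**Working it through.** **Inputs**, all from the Sample size calculation section: p1 = 0.20, p2 = 0.15, power 80%, significance level 5%, dropout 20%, 1:1 allocation, 1200 per group. Two-sided testing is an assumption, tested in step 3.

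**1. Evaluable number needed per group.** With z(0.975) = 1.960, z(0.80) = 0.842 and mean proportion 0.175:

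- Pooled variance: n = [1.960·√(2·0.175·0.825) + 0.842·√(0.20·0.80 + 0.15·0.85)]² / 0.05² = 905.4, rounded up to 906.
- Unpooled variance: n = (1.960 + 0.842)²·(0.16 + 0.1275) / 0.05² = 902.6, rounded up to 903.
- Arcsine: 902.3.
- Pooled with continuity correction: 945.

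None of these is near 1130.

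**2. Reproducing the plan's 1130.** Divide by 1 − 0.20:

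| Formula | Evaluable | ÷ 0.8 |
|---|---|---|
| Pooled | 906 | 1133 |
| Unpooled | 902.6 | 1128 |
| Arcsine | 902.3 | 1128 |
| Continuity-corrected | 945 | 1182 |

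The first three rows bracket 1130. In reverse, 1130 × 0.8 = 904. One other route also lands close: the continuity-corrected 945 multiplied by 1.2 gives 1134. That route, too, reaches 1130 only after dropout has been added.

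**3. Does another reading give 1130 before dropout?** One-sided testing at 5% needs 714 (753 with continuity correction), which inflates to 893 (942). Neither comes near 1130. No variant tried gives 1130 as an uninflated count.

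**4. What the literal wording would imply.**

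- 1200 × 0.8 = 960 evaluable, and 1130 − 960 = 170 short per group.
- 1200 enrolled would leave 1130 evaluable only if dropout were at most 1 − 1130/1200 = 5.8%.
- 1130 evaluable at 20% dropout would require 1130/0.8 = 1412.5, so 1413 per group.
- Power with 1130 evaluable would be 87.9%, not the stated 80%.

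**5. What the plan delivers on its own inputs.** Power = Φ{[0.05·√n − 1.960·√(2·0.175·0.825)] / √0.2875}.

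- n = 906: 80.0%.
- n = 960: 82.3% (80.6% with continuity correction).

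So 960 evaluable exceeds 906 by 54 and 945 by 15. The 1200 to be randomised exceeds 1133 by 67 and 1182 by 18.

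**The case against.** The strongest reply is that nothing in the design is wrong. Dropout stands in the same parenthesis as power and significance level, so a reader can see that it was applied. One adjective is misplaced, while the target, the allocation and the 80% power claim all survive. That is right as far as the design goes, and it limits the point to the stated requirement. It does not remove the point, because the wrong word sits on the figure that says how many analysed patients are enough.

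A reader might infer from the label that the trial misses its own requirement, is underpowered, or should enrol 1413 per group. The documents do not support this. It follows only if 1130 is taken as a true evaluable count, which the stated inputs rule out.

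A reader might also infer that decisions to stop or extend recruitment rest on the wrong figure, since the Discussion reports slow and interrupted inclusion. The article ties no such decision to 1130; its working target is 1200 per group.

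Two technical objections concern the replacement figures. First, neither the sidedness nor the formula is stated. This stands, and the continuity-corrected values are given for that reason. Second, the analysis section plans mixed models for clustering of patients within physician, which these calculations ignore; 960/906 = 1.06 leaves about 6% of room for variance inflation. This carries little weight, because patients and not physicians are randomised, so the design effect of a cluster-randomised trial does not arise. The assumption should still be stated.

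**Conclusion.** The concern holds as a mislabelled figure. On the stated inputs about 903 to 906 evaluable patients per group are needed (945 with continuity correction), and 1130 is the number to randomise after allowing for 20% dropout. The word evaluable overstates the requirement by 224 per group against 906, or by 185 against 945, and makes the section inconsistent with its own dropout rate and target.

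It is not a power shortfall: the planned enrolment covers the need under either formula. The conclusion that 1130 includes dropout does not depend on the choice between them. The replacement figures rest on a two-sided 5% level, a simple comparison of two proportions, independent patients, and the article's 20% and 15% rates and 20% dropout.

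**What to change.** Restate the requirement in the Sample size calculation section along these lines, once the trial statistician has confirmed the sidedness and formula used:

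> About 906 evaluable patients per group are needed to detect a reduction from 20% to 15% (two-sided 5% level, 80% power, two-proportion formula without continuity correction, clustering ignored). Allowing for 20% dropout, about 1133 per group must be randomised. The target of 1200 per group is expected to yield 960 evaluable patients per group and about 82% power (about 81% with continuity correction).

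If the continuity-corrected formula was used, the corresponding figures are 945 evaluable and 1182 to randomise per group, still within 1200.

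The cost is a short rewording. Enrolment, allocation and analysis do not change.

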### Data analysis / statistical analysis

The effect evaluation will be analyzed according to the intention to treat principle. The difference in primary and secondary outcome variables between the intervention and the control group will be assessed using mixed effect models to account for the clustering of patients within physician and/or repeated measurements. A logit link function will be used for the binary outcomes and an identify link for numerical outcomes. A likelihood-based approach will be applied to account for missing outcomes variables, assuming missingness at random (MAR). The stratification variable (hospital location), variables related to missing data/drop outs (to ensure MAR) and variables related to the outcome such as age and sex, will be included in the fixed part of the models.

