In view of the considerations above, the aim of this study is to investigate whether the continuous use of a CDSS decreases the number of hospital readmissions in older patients who previously have had an unplanned probably medication-related hospitalization according to the triggerlist from The Dutch multidisciplinary guideline for polypharmacy in older patients [13].

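### The logit-or-identity link rule does not fit time to hospital readmission, a secondary outcome censored in 80 to 85% of patients

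*Protocol article*

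**What the plan says.** In the protocol article, Data analysis / statistical analysis sets the model class: "The difference in primary and secondary outcome variables between the intervention and the control group will be assessed using mixed effect models". It then sets the link: "A logit link function will be used for the binary outcomes and an identify link for numerical outcomes". The word printed before the second link is plainly meant as identity. Incomplete outcomes are covered by a likelihood-based approach under missingness at random. The section names no censored-data model, no count model and no term for follow-up time, and it exempts no outcome.

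Secondary outcomes lists "mortality within 1 year after study inclusion", then "II) the number of emergency department visits; (III) the number of nursing home admissions", then "IV) time to hospital readmission; and (V) the number of hospital readmissions after 30 and 180 days". Quality of life and societal costs are added after these.

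The primary outcome is binary: "The primary outcome of this study is hospital readmission within 1 year after study inclusion". Sample size calculation plans for a reduction from 20% to 15% with 20% dropout and 1200 patients per group.

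**The concern.** Time to readmission is right-censored. A patient who is not readmitted within the year has a time known only to exceed the follow-up. A linear model with an identity link has no place for that information, so the analyst must do one of two things:

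- **Leave the time missing.** With a single outcome per patient, likelihood under missingness at random then reduces to an analysis of the readmitted patients. The missingness depends on the unseen value itself, so the assumption fails. The comparison also conditions on an event that the intervention is meant to prevent.
- **Enter the last follow-up time as if it were the readmission time.** The result then mixes readmission with length of follow-up, which dropout and death both shorten.

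At stake is whether this secondary outcome can show the effect the trial is designed to find. The counts fall under the same link rule without a follow-up term, which is a milder weakness.

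**Working it through.** **Inputs.** From Sample size calculation: 20% versus 15% readmitted, 20% dropout, 80% power, 5% significance level (taken as two-sided), 1200 per group. From Primary outcome: one year, taken as 365 days. Assumed here: constant hazards, loss independent of readmission, no physician clustering.

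**The plan's own figure.** Two proportions, no continuity correction:
n = [1.96 × √(2 × 0.175 × 0.825) + 0.8416 × √(0.20 × 0.80 + 0.15 × 0.85)]² / 0.05² = 906 per group; 906 / 0.8 = 1133. The article gives 1130, so the inputs are read correctly.

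**Hazards.** −ln(0.80) = 0.223 and −ln(0.85) = 0.163 per year; hazard ratio 0.728.

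**Reading A: linear model on the readmitted only.** For an exponential time truncated at T, the mean is 1/λ − T·e^(−λT)/(1 − e^(−λT)).
- Control: 365/0.2231 − 365 × 0.80/0.20 = 175.7 days.
- Intervention: 365/0.1625 − 365 × 0.85/0.15 = 177.6 days.
- Difference: 1.8 days. The SD is about 105 days in each arm.
- With 1200 × 0.8 = 960 per group, 192 and 144 patients are readmitted. SE = 105 × √(1/192 + 1/144) = 11.6 days. Two-sided power is 5.3%, in effect the significance level.

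**Log-rank on the same data.** Events: 192 + 144 = 336. |ln 0.728| × √(336/4) = 2.91; 2.91 − 1.96 = 0.95; power 82.8%.

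**Reading B: non-readmitted entered at last follow-up.** Simulated, 1200 per group, 2000 trials per scenario. The loss patterns that differ by arm are assumptions.

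| Scenario | A: readmitted only | B: last follow-up | Log-rank |
|---|---|---|---|
| True effect, no loss: power | 5% | 82% | 90% |
| True effect, 20% loss per arm: power | 5% | 45% | 86% |
| No effect, loss 25% control, 15% intervention: type I error | 7% | 96% | 5% |

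In a fourth scenario, with a true benefit and loss of 15% in control and 25% in intervention, reading B gives a mean difference of −9 days. The sign is reversed.

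**Counts.** Poisson counts with the same rates, identity link and no follow-up term, against a rate comparison using person-time:
- 20% loss per arm: type I error 5%; power 88%, against 88 to 89% for the rate comparison. The mean difference shrinks from −0.061 to −0.054 (0.054/0.061 = 0.89, so about 10% attenuation).
- No effect, loss differing by arm: type I error 10% at 25% versus 15% and 26% at 30% versus 10%. The rate comparison stays at 5%.

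**The case against.** The best defence is that the article sets links for binary and numerical outcomes, and that a time-to-event outcome is commonly a third class whose method is left to a fuller plan. The text does not say that every numerical outcome without exception takes the identity link. It also does not say that patients without a readmission are dropped, so 5% power belongs to one possible reading. This is fair as far as it goes. However, the opening sentence covers primary and secondary outcomes without exception, and only two links are offered. That is a stated rule which does not fit a named outcome, and not merely an absent detail. The other reading does better than 5%, but it loses about half its power under the plan's own dropout rate.

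Several stronger readings are tempting and are not supported:

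- **A reader might infer that the count analyses are equally invalid.** With similar follow-up in both arms they keep their type I error and nearly all their power. Bias needs follow-up to differ by arm, and the documents give no such difference. Because these outcomes come from electronic records, leaving the study need not end their capture.
- **A reader might infer from the Background's aim, "whether the continuous use of a CDSS decreases the number of hospital readmissions in older patients", that no endpoint answers it.** The primary outcome is one-year readmission, and Sample size calculation states the aim as a lower readmission rate.
- **A reader might infer that the 30- and 180-day periods start on the ward, before readmission is possible.** For that outcome the article does not state the time origin.
- **A reader might infer that the main result is at risk.** The primary outcome is binary and takes the logit link.

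**Conclusion.** The point stands for time to readmission. As written, the rule yields an analysis that either cannot see the planned effect (about 5% power against about 83% with 960 per group) or depends on follow-up (45% against 86% with 20% loss per arm, and biased if loss differs between arms). Without any loss, the second reading comes close (82% against 90%), but the plan itself expects loss.

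The figures rest on constant hazards, independent loss and no physician clustering. The unequal-loss scenarios are illustrations, and the article gives no mortality rate. For the counts, a follow-up term is a safeguard with little gain when follow-up is similar in both arms. Neither the primary analysis nor the sample size is touched, so this is a moderate correction to a secondary outcome.

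**What to change.** Exempt time to hospital readmission from the link rule and name a censored-data method. One suitable choice is a Cox model for first readmission, adjusted for or stratified by hospital location, with a frailty term or robust errors for physician clustering, censoring at withdrawal, and death handled as a competing event and shown in cumulative incidence curves. Keep the identity link for outcomes that suit it, such as quality-of-life scores and, if wished, costs.

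As a lesser change, analyse emergency department visits, nursing home admissions and numbers of readmissions with a log-link count model, with log follow-up time as offset. This protects against bias if deaths or dropout differ by arm.

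The cost is wording. The article already takes its secondary outcomes from electronic records, so no new data collection appears to be needed. If a fuller plan already names such methods, it is enough to bring the two texts into line. Make the change before outcome data are examined by arm.
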